### Study recruitment and randomization

Recruitment will occur in the Greater Toronto Area (total population 4.5 million) in urological oncology clinics and through presentations and/or information stands [52] set-up at local PCa support group meetings. These peer-support meetings often include men who have been recently diagnosed and are considering various treatments for PCa, including RP. Men who self-identify as eligible will receive further verbal and written information about the study. Those deemed eligible and are interested will be asked to provide written consent.

Participants will be 1:1 randomized to the UC and APFX groups, stratified by age (±60 years). Blinded allocation of the participants to their treatment groups will be performed via a process consisting of placing the intervention assignments into opaque envelopes, sealing and shuffling the envelopes, and sequentially numbering them with each new participant receiving an envelope in sequence of recruitment. The envelopes will be opened by the research coordinator with the participant following the baseline assessment, prior to RP Fig. 1.

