### Study population/participants

Eighty-eight participants will be recruited for this trial. We anticipate an attrition rate of 20 % by the 26-week follow-up assessment to yield 70 participants (35 participants per group) for main efficacy estimate analyses that is aligned with recommended pilot and feasibility study sample sizes for treatment effect estimates [47–49]. *Inclusion Criteria*: Patients that: i) have localized PCa who have consented for RP (open retropubic, laparoscopic, or robot-assisted laparoscopic); ii) are between the ages of 40 and 80 years; and iii) are proficient in English. *Exclusion Criteria*: Patients that: i) are diagnosed with a known neurological disease, autoimmune connective tissue disorder; ii) have prior experience with pelvic floor training by a healthcare provider; iii) have uncontrolled hypertension; iv) have diagnosed chronic obstructive pulmonary disease (COPD) and/or chronic restrictive respiratory disease; v) have a history of inguinal herniation; or vi) have hypertonic pelvic floor muscles upon baseline evaluation. Pelvic floor tonicity will be assessed by a specially trained pelvic floor physiotherapist via digital rectal examination. Hypertonic pelvic floor is determined by the physical examination findings of extrapelvic musculoskeletal and connective tissue examination, as well as the elements of patient history [50]. These patients who exhibit levator ani hypertonicity (tension myalgia) will be excluded as they can experience pelvic, urogenital, and rectal pain; tightness and spasticity; and adverse effects on sexual, urinary, and bowel function that may be exacerbated with contraction-based pelvic floor training [51, 52].

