### Body composition

Research has shown that men who are overweight reported lower post-operative urinary function [72, 73]. Body mass index (kg/m^2^) will be calculated using participant’s height (m) and weight (kg). Body fat percentage will be assessed by bioelectrical impedance analysis (Tanita© 3000A, Tokyo, Japan). Waist to hip circumference ratio will be measured according to the World Health Organization protocol [74]. Waist circumference will be measured with the measuring tape positioned at the midpoint between lowest margin of the last palpable rib and the top of the iliac crest and hip circumference will be measured at the widest girth of the gluteal region.

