## Statistical analysis

Participant characteristics at baseline will be compared using independent sample t-tests or chi-square tests. We will report retention and compliance rates for the sample and their associated 95 % CI as well as reasons for non-participation of eligible patients. To calculate outcome capture, we will calculate the proportion of participants who have complete data on each outcome at each time point divided by the total number of study participants. Estimates of efficacy (Group and Time main effect, as well as Group x Time interactions) will be analyzed using a repeated-measure analysis of covariance (ANCOVA), controlling for the baseline value of the outcome of interest. We will examine the effect size (Cohen’s d) of the intervention on the clinical outcomes by dividing the observed mean between-group difference in change in the outcome measure from baseline to follow-up (UC vs. APFX) by its standard deviation.

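### Randomisation is said to be stratified by age, but the envelope procedure described does not use age, and the stated ANCOVA leaves the stratification factor out

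*Protocol article*

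**What the plan says.** In the protocol article, the section Study recruitment and randomization makes two statements in consecutive sentences.

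- The design claim: "Participants will be 1:1 randomized to the UC and APFX groups, stratified by age (±60 years").
- The procedure: assignments go into opaque envelopes, followed by "sealing and shuffling the envelopes, and sequentially numbering them with each new participant receiving an envelope in sequence of recruitment". The research coordinator opens the envelope with the participant after the baseline assessment and before surgery.

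The section does not mention a separate envelope series for each age group, and it does not mention blocks. The symbol ± does not say which stratum a man aged exactly 60 joins. Such men are eligible, since participants "are between the ages of 40 and 80 years".

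The section Statistical analysis says the efficacy estimates "will be analyzed using a repeated-measure analysis of covariance (ANCOVA), controlling for the baseline value of the outcome of interest". The model terms named are group, time, their interaction and the baseline outcome. Age is not among them.

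**The concern.** Stratified allocation needs the participant's stratum to determine which sequence he draws from. In the procedure described, a man's envelope is fixed by his place in the order of recruitment. A coordinator who followed those steps exactly would carry out unstratified randomisation, and the trial would then report it as stratified.

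Two things are at stake. One is accurate reporting of the design, which matters more than usual because the pilot's primary objective is to test the feasibility of a full-scale trial of similar design, so the allocation description may be carried forward. The other is precision: age balance would be left to chance in a sample of 88, and the stated model has no age term to absorb an imbalance.

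**Working it through.** **Inputs**

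- Total randomised, from Study population/participants: "Eighty-eight participants will be recruited for this trial". At 1:1 this is 44 per arm.
- Evaluable number, same section: "We anticipate an attrition rate of 20 % by the 26-week follow-up assessment to yield 70 participants (35 participants per group").
- Size of an age stratum: not given. Assumed to be m = 20 to 44 men; the other stratum has 88 − m.

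**Reproducing the plan's figure.** 70 / (1 − 0.20) = 87.5, rounded up to 88. The target reproduces, and nothing below changes it.

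**Step 1. One shuffled deck of 44 UC and 44 APFX envelopes.** Let X be the number of men in the stratum who draw APFX. X is hypergeometric with population 88, 44 APFX envelopes and m draws. The between-arm difference in the stratum is D = 2X − m, and

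SD(D) = 2 × √[44 × (m/88) × (1 − m/88) × 44/87].

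- m = 20: 2 × √(44 × 0.2273 × 0.7727 × 0.5057) = 2 × 1.98 = 3.95
- m = 30: 2 × 2.24 = 4.47
- m = 44: 2 × √(44 × 0.5 × 0.5 × 0.5057) = 2 × 2.36 = 4.72

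Exact tail probabilities:

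| m | SD of D | P(abs. D ≥ 4) | P(abs. D ≥ 6) | P(abs. D ≥ 8) |
|---|---|---|---|---|
| 20 | 3.95 | 45% | 20% | 7% |
| 21 | 4.02 | 32% | 13% | 4% |
| 29 | 4.43 | 37% | 17% | 7% |
| 30 | 4.47 | 50% | 26% | 11% |
| 35 | 4.62 | 38% | 19% | 8% |
| 44 | 4.72 | 52% | 29% | 13% |

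Odd and even sizes must both be included. D has the same parity as m, so for odd m a difference of 6 or more means 7 or more, which is less likely. Over all m from 20 to 44, P(6 or more) runs from 13% (m = 21) to 29% (m = 44). Because the deck forces 44:44 overall, a surplus in one stratum is matched by an equal deficit in the other.

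**Step 2. Two shuffled sets without blocks.** If each stratum had its own set of 88 envelopes (44 + 44), the imbalance within each stratum would have the same distribution as in Step 1. If each had 44 envelopes (22 + 22) and the strata turned out to be 35 and 53, the expected absolute difference in the smaller stratum would be 2.2 men, and the other set would be 53 − 44 = 9 envelopes short. A shuffled set guarantees balance only if it is used up exactly.

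**Step 3. Separate series in permuted blocks.** With blocks of 4 (an assumption), the difference within a stratum cannot exceed 2 men.

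**Step 4. Effect on the efficacy estimate.** Dividing SD(D) by 44 gives the SD of the between-arm difference in age mix. For strata of 26 to 44 men this is 9.8 to 10.7 percentage points. If the strata differ by 0.2 to 0.5 SD on an outcome (an assumption), the chance shift in the treatment difference has an SD of about 0.2 × 0.10 = 0.02 to 0.5 × 0.107 = 0.05 outcome SD. The standard error at 35 per arm is √(2/35) = 0.24. Adding 0.05 in quadrature gives √(0.239² + 0.054²) = 0.245, an increase of about 2.5%. At 0.02 the increase is about 0.4%.

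**The case against.** The strongest reply is that the article never says there is only one set of envelopes. A reader might infer that the trial cannot have stratified and would be claiming a property it lacks. The text does not establish that: shuffling and numbering within each age group, with each man taking the next envelope in his own group, can be reconciled with both sentences. A condensed article may also leave separate series and blocks to the full protocol, and silence on blocks is not a statement that there are none. This stands as a limit on the point. It does not remove it, because the article sets out the procedure step by step, its natural reading is one sequence in recruitment order, and no step refers to age.

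A second reply is that the full covariate list usually belongs in the SAP, which is not shown and could include age. That is fair, so the covariate remark rests only on the model as stated. If stratification was in fact carried out, omitting the stratum usually makes standard errors slightly conservative and does not bias the estimate.

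A third is that little depends on this numerically. A shuffled 44 + 44 deck is valid randomisation with exact overall balance, feasibility is the primary outcome, and none of the feasibility measures depends on age balance between arms. This stands in full and determines the severity.

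A reader might also infer that body mass index should join the model, since the Body composition section says "Research has shown that men who are overweight reported lower post-operative urinary function". That sentence reports an association. Choosing body mass index as a covariate is optional and answers no defect here. Nor does the text show a fault in who prepares the envelopes: it says only who opens them.

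**Conclusion.** The point holds as an inconsistency to be reconciled, with low to moderate severity. The claim of age stratification and the procedure given for it do not match: followed as written, the procedure leaves age balance to chance, and the stated ANCOVA, "controlling for the baseline value of the outcome of interest", does not compensate.

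The Step 1 imbalance probabilities rest on one shuffled deck, which is an inference from the wording, and on an assumed stratum size. The effect on the estimates rests on the further assumption that the age strata differ by 0.2 to 0.5 SD on the outcome. Under these, the efficacy estimates remain unbiased over randomisations and lose only a few per cent of precision at most. The documents do not support reading this as a flaw that invalidates the randomisation or threatens the trial's primary objective.

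**What to change.** 1. In Study recruitment and randomization, describe one separately numbered envelope series for each age stratum, each built in permuted blocks, with each man taking the next envelope in his own stratum's series. If this is what was intended, it is a change of wording only; otherwise the envelopes must be prepared accordingly before enrolment.
2. Replace ±60 with a rule that places a man aged exactly 60 in one stratum.
3. In Statistical analysis, add the age stratum as a fixed covariate in the efficacy ANCOVA.
4. If separate series are not used, delete the word stratified and still adjust for age.

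The cost is the envelope preparation, a few words of text and one model degree of freedom. The sample size stays at 88, and no visits or measurements are added.

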## Study arms

The two groups will begin participation in their respective interventions immediately following post-operative catheter removal until 26-weeks post-operatively. The physiotherapist assessment of pelvic floor muscle activity and strength will be assessed during each visit in order to optimize the quality of the contractions. Instructions to correctly contract their pelvic floor will be provided verbally and with biofeedback via the Modified Oxford Scale (MOS). Grading of this scale is described below. The research coordinator, who is a Registered Kinesiologist with training and experience in pelvic floor strengthening, Pfilates, and Hypopressives, will be providing the intervention prescription for both study arms and will communicate weekly with the participants to support and quantify program compliance (# of completed contractions/# prescribed contractions), facilitate prescribed progression, and address any barriers to program participation. Furthermore, both groups will receive a manual that includes detailed information and instructions relevant to their training regimens (Tables 1 and 2).

**Table 1 Tab1:** UC, conventional pelvic floor muscle exercise prescription

Week	Positions	Reps each position	Sets	Contractions daily
1 & 2	Lying and sitting	15-20	2-3	30-60
3 & 4	Lying, sitting, and standing	30-40	2-3	60-120
5 & 6		40-50	3	120-150
7 – 26		50-60	3	150-180

**Table 2 Tab2:** Advanced pelvic floor muscle exercise prescription

Week	Exercise	Position/pose	Reps	Sets	Hold (sec)	Pulses (Pfilates only)
1	Kegels	Lying and sitting	10-12	3	5-10	
	Pfilates	Butterfly	5	3	3-5	5
	Hypopressive	Diaphragmatic breathing (lying)	3	3	Fully inhale and exhale	
2	Kegels	Lying and sitting	10-12	3	5-10	
	Pfilates	Butterfly	5	2	5-8	5
		Bridge	5	2	3-5	5
	Hypopressive	Standing	3	3	5-10	
3	Kegels	Lying, sitting, and standing	10-12	2	8-10	
	Pfilates	Butterfly	5-10	2	8-10	5-10
		Bridge	5-10	2	5-8	5-10
		Lunge	5-10	2	3-5	5-10
	Hypopressive	Standing	3	2	10-15	
		Kneeling	3	2	5-10	
4	Kegels	Lying, sitting, standing	10-12	3	8-10	
	Pfilates	Butterfly	8-10	2	10	8-10
		Bridge	8-10	2	10	8-10
		Lunge	8-10	2	5-8	8-10
	Hypopressive	Standing	3	1	10-20	
		Kneeling	3	1	10-15	
		Downward kneel	3	1	10-15	
5	Kegels	Lying, sitting, standing	10-12	3	8-10	
	Pfilates	Butterfly	10-12	2	10	10-12
		Bridge	10-12	2	10	10-12
		Lunge	10-12	2	10	10-12
	Hypopressive	Standing	3	1	10-30	
		Kneeling	3	1	10-20	
		Downward Kneel	3	1	10-20	
		Sitting	3	1	10-15	
6-12	Kegels	Lying, sitting, standing	10-12	3	8-10	
	Pfilates	Butterfly	10-12	3	10	10-12
		Bridge	10-12	3	10	10-12
		Lunge	10-12	3	10	10-12
	Hypopressive	Standing	3	1	10-30	
		Kneeling	3	1	10-30	
		Downward Kneel	3	1	10-30	
		Sitting	3	1	10-30	
12-24	Kegels	Lying, sitting and standing	10-15	3	8-10	
	Pfilates	Butterfly	10-15	3	10	10-15
		Bridge	10-15	3	10	10-15
		Lunge	10-15	3	10	10-15
	Hypopressive	Standing	3	1	10-30	
		Kneeling	3	1	10-30	
		Downward Kneel	3	1	10-30	
		Sitting	3	1	10-30	

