More recent PFMX paradigms incorporate techniques aimed at optimizing pelvic floor muscle responsiveness and contraction quality through the utilization of other regional muscles. One such approach is “Pfilates” (‘*P*elvic *F*loor P*ilates*’) that incorporates the fundamental elements of Pilates (a form of exercise that focuses on core strength, stability, flexibility, and muscle control, as well as posture and breathing) [39, 40] with targeted pelvic floor activation [41]. Pfilates includes several static poses that activate the TrA, hip adductors, gluteal, and pelvic floor muscles with instructions to pulse (small range of motion) with short, maximal effort contractions of the engaged muscles. A recent study by Culligan et al. [40] demonstrated comparable improvements in pelvic floor strength measured by perineometry after 12 weeks of conventional PFMX versus Pilates in 62 women with little or no pelvic floor muscle dysfunction. Although UI was not measured, this study suggests that Pilates may produce similar benefits for UI as traditional PFMXs.

Another novel approach to PFMXs is known as ‘Hypopressive’ exercises. Hypopressive exercises emphasize engaging the TrA with conscious coordination of the diaphragm with breathing that is hypothesized to increase muscle tone of the pelvic floor muscles and subsequently cause urethral constriction [30, 42–45]. While executing the prescribed Hypopressive techniques, the use of deep breathing followed by a brief breath-hold causes relaxation of the diaphragm, decrease in intra-abdominal pressure, and a reflex contraction of the pelvic floor muscles, unconsciously maximizing a contraction and consequently improving re-conditioning of these muscles [43, 45]. Caufriez [46] communicated this technique in 1997 and described the steps as follows: slow diaphragmatic inspiration, followed by total expiration and, after glottal closure, a gradual contraction of the abdominal wall muscles, with superior displacement of the diaphragm cupola (referred to as diaphragmatic aspiration). There is significant attention drawn to the distension of the ribs, breathing, and body positions, so that even though one is aware of their pelvic floor, it is an unconscious movement [30, 38, 43]. Early research on the effects of Hypopressive exercise programs have demonstrated increased tonic activity, strength, and size of the pelvic floor muscles via ultrasonography imaging [44].

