## Methods

This study is a 2-arm, pilot randomized controlled trial (RCT) that compares the effect of a conventional PFMX program, considered usual care (UC), to an advanced pelvic floor exercise program (APFX) including Pfilates, and Hypopressive for the management of UI after RP for PCa. The primary objective of this study is to assess the feasibility of conducting a full-scale RCT of similar design. Feasibility will be determined via recruitment success, participant retention, outcome capture, intervention adherence, and prevalence of adverse events. Our secondary objectives are to compare the efficacy of APFX to UC in UI, pelvic floor strength, erectile function, and QoL after RP. This study will be conducted at the Wellness and Exercise for Cancer Survivors (WE-Can) program at the Princess Margaret Cancer Centre. WE-Can is a multidisciplinary team of physicians, physiotherapists, kinesiologists, and other exercise professionals that provide exercise and physical activity programming for cancer survivors.

This study has been approved by the ethics boards of the participating institutions and all participants will be asked to provide voluntary and informed consent.

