### Advanced Pelvic Floor Exercise (APFX)

Participants will start with the introduction of basic PFMX (comparable to UC) with a gradual integration of Pfilates and Hypopressive exercises until week 12. The Pfilates exercises will progressively integrate postures that engage and activate supportive abdominal muscles including the TrA, hip adductors, and gluteals. During each pose, participants will be asked to perform a series of pulses within a small range of motion while maximally contracting their pelvic floor simultaneously. Similarly, the Hypopressive techniques are gradually integrated in the prescription and progressed over 12 weeks. These exercises focus on diaphragmatic breathing and TrA activation in various static postures. Participants are instructed to perform three successive slow diaphragmatic inspirations, followed by a total expiration and apnea (breath hold). Each apnea will be performed for approximately 10–30 seconds while activating their TrA and intercostal muscles and rising of their hemidiaphragm [45]. APFX participants will be gradually progressed in postures and repetition volume, varying between PFMX, Pfilates, and Hypopressives. Weeks 13–26 comprise the maintenance stage where patients will maintain their prescription until the end of the trial. A detailed week-by-week description of the program is provided in Table 2 and Appendix A. Total APFX contraction volume reflects the volume prescribed in the UC group following post-operative weeks.

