## Feasibility assessment

Prior pelvic floor training trials in PCa patients undergoing RP have observed recruitment rates of 21-70 % [21]. We will measure recruitment success through participant recruitment per week and record reasons for non-participation from those who inquire about the study and are eligible to participate but refuse. Adherence to the UC and APFX program will be measured through a logbook that is included in their respective manuals as well as a logbook completed by the research coordinator during the weekly telephone communication that will compare prescribed to completed volume of contractions. Retention will be assessed by measuring attrition throughout the intervention period and at each assessment. We will monitor and record non-severe and severe adverse events that occur to participants during the course of this study using the National Cancer Institute Common Terminology Criteria for Adverse Events version 4.0 [53].

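### The single contraction-count measure of adherence is nearly insensitive to omission of the Hypopressive exercises, one of the two novel parts of the APFX programme

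*Protocol article*

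**What the plan says.** The Methods section makes feasibility the primary objective and lists adherence among its measures: "Feasibility will be determined via recruitment success, participant retention, outcome capture, intervention adherence, and prevalence of adverse events". Study arms gives the formula once for both arms: the coordinator's weekly contact serves to "quantify program compliance (# of completed contractions/# prescribed contractions". Feasibility assessment describes the same quantity, taken from a participant logbook and a coordinator logbook "that will compare prescribed to completed volume of contractions". Statistical analysis then commits to the output: "We will report retention and compliance rates for the sample and their associated 95 % CI".

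No separate adherence figure for Kegels, Pfilates or Hypopressives is stated. Nor does the article say whether a Hypopressive repetition or a Pfilates pulse is a contraction for this purpose.

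On Hypopressives, the APFX section says "These exercises focus on diaphragmatic breathing and TrA activation in various static postures", and Appendix A builds each repetition around a timed breath-hold. The Background describes the pelvic floor response in these words: "so that even though one is aware of their pelvic floor, it is an unconscious movement".

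**The concern.** A ratio summed over exercise types weights each type by its number of repetitions. Hypopressives are prescribed as a few long holds, whereas Kegels and Pfilates are prescribed in tens of repetitions. The count therefore gives Hypopressives little weight, although they are one of the two elements that distinguish APFX from usual care and are named in the trial's rationale.

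The pilot is meant to inform a larger trial of the combined programme. With this measure alone, it could report adherence above 90% when one of the two novel components was not done at all. That would affect how uptake is judged and how a null or weak efficacy estimate is read. If the weekly calls record only totals, the component information may not be recoverable later.

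**Working it through.** **The plan's own figures.** The article prints no adherence percentage and no APFX contraction total. The nearest figure is the daily count in Table 1. Repetitions × sets, without multiplying by position, reproduces every row:

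- weeks 1–2: 15×2 = 30 to 20×3 = 60
- weeks 3–4: 30×2 = 60 to 40×3 = 120
- weeks 5–6: 40×3 = 120 to 50×3 = 150
- weeks 7–26: 50×3 = 150 to 60×3 = 180

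**Inputs from Table 2, week 6 onward.**

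- Kegels (K), "Lying, sitting, standing 10-12 3 8-10": 10–12 × 3 sets = 30–36 if counted as in Table 1, or 90–108 if repeated in each of three positions. In the last row (10–15 repetitions) these become 30–45 or 90–135.
- Pfilates (P), for example "Butterfly 10-12 3 10 10-12", in three poses: 3 × 10–12 × 3 = 90–108, and 90–135 in the last row. Appendix A makes the pulses a further phase equal in number to the repetitions, so counting them doubles P to 180–216 and 180–270.
- Hypopressives (H): 4 poses × 3 repetitions × 1 set = 12.

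Table 2 prints no daily frequency. If the three types are done equally often, frequency cancels from the ratio.

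**Score with no Hypopressives and all else completed:** (K + P)/(K + P + H), counting one breath-hold repetition as one contraction.

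| Counting rule | Weeks 6–12 | Last row |
|---|---|---|
| Kegels once, no pulses | 120/132 = 90.9% to 144/156 = 92.3% | 120/132 = 90.9% to 180/192 = 93.8% |
| Kegels per position, no pulses | 180/192 = 93.8% to 216/228 = 94.7% | 180/192 = 93.8% to 270/282 = 95.7% |
| Kegels once, pulses added | 210/222 = 94.6% to 252/264 = 95.5% | 210/222 = 94.6% to 315/327 = 96.3% |
| Kegels per position, pulses added | 270/282 = 95.7% to 324/336 = 96.4% | 270/282 = 95.7% to 405/417 = 97.1% |

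Hypopressives are thus at most 12/132 = 9.1% and at least 12/417 = 2.9% of the count.

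**Weeks 1–5.** The lowest value is week 3, Kegels once and no pulses: K = 20, P = 30, H = 12, so 50/62 = 80.6%. The highest is week 4, per position with pulses: 228/237 = 96.2%.

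**Over 26 weeks** (rows weighted by weeks; last row taken as weeks 13–26; common factor of 7 days omitted).

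- Lowest (Kegels once, no pulses, lower limits): K = 140 + 7×30 + 14×30 = 770; P = 173 + 7×90 + 14×90 = 2063; H = 51 + 7×12 + 14×12 = 303. Score 2833/3136 = 90.3%.
- Highest (per position, pulses added, upper limits): K = 432 + 7×108 + 14×135 = 3078; P = 454 + 7×216 + 14×270 = 5746; H = 303. Score 8824/9127 = 96.7%.

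Table 2 lists week 12 in two rows and ends at week 24, while the APFX section runs to week 26. Those passages need reconciling, but with a 12-week last row the range is still 90.3–96.6% (2593/2872 to 8014/8293).

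**Contrast: Pfilates omitted, all else done, 26 weeks:** (K + H)/(K + P + H). The highest is 2553/4616 = 55.3% (per position, no pulses, lower limits). The lowest is 1353/7099 = 19.1% (Kegels once, pulses added, upper limits).

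**By component,** the man who omits only Hypopressives would show Kegels 100%, Pfilates 100%, Hypopressives 0%.

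**The case against.** The strongest reply is that this is a condensed article. Each arm has its own manual and logbook, Table 2 itemises the prescription by exercise and pose, and the coordinator speaks to every participant weekly. Component data may well be recorded, and a breakdown may be planned in a document not shown. That stands, and it rules out saying that the pilot cannot learn about Hypopressive uptake. It does not remove the point, because the article prints a specific formula and that formula has the property shown.

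A common unit is also defensible: the arms are meant to have comparable volume, so completed over prescribed contractions is a sensible between-arm measure. This stands too, and is why the ratio should be kept. Nor is it incoherent to count a Hypopressive repetition as a contraction, since the Background describes a reflex contraction of the pelvic floor. The article simply does not say which applies.

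A reader might infer three stronger things that the document does not support.

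- That uptake of both novel components is hidden. It is not: omitting Pfilates pulls the score down to 19–55%.
- That the count is driven by the conventional exercise. Under Table 1's own counting, Pfilates in weeks 6–12 is 90/132 = 68% to 108/156 = 69% of the total and Kegels about 23%. Even when Kegels are multiplied by position they only equal Pfilates (without pulses).
- That the decision on a full trial rests on this number. The article states no adherence threshold, and adherence is one of five feasibility measures.

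**Conclusion.** The point holds for Hypopressives. The stated measure barely responds when they are dropped: about 91–97% from week 6 and 90–97% over 26 weeks. In some of weeks 1–5 the score can fall to about 81%, so omission is less well hidden then. These figures assume that each breath-hold repetition counts as one contraction and that all Kegels and Pfilates are completed. If breath-holds are not counted, the score is 100% throughout. The conclusion is the same under all four counting rules.

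The pooled figure by itself therefore does not show whether the combined programme was taken up. This is a weakness in a stated primary feasibility measure, worth correcting because correction is cheap. It does not invalidate the pilot.

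**What to change.** Keep the pooled ratio for comparing arms. In Study arms and Feasibility assessment, state whether a Hypopressive repetition and a Pfilates pulse each count as a contraction. In Statistical analysis, add that APFX adherence will also be computed as completed over prescribed repetitions separately for Kegels, Pfilates and Hypopressives, each with a 95% CI, and that the conclusion on APFX adherence will be drawn from these component figures.

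The existing logbooks and weekly calls can supply the data, and the exercise prescription is unaffected. The cost is slightly more recording (three lines instead of one, if the logbooks do not already separate the exercises), three proportions in the report, and a possibly less favourable adherence figure.
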